## Abstract

**Background:**

Intrathecally administered morphine is effective as part of a postoperative analgesia regimen following major hepatopancreaticobiliary surgery. However, the potential for postoperative respiratory depression at the doses required for effective analgesia currently limits its clinical use. The use of a low-dose, prophylactic naloxone infusion following intrathecally administered morphine may significantly reduce postoperative respiratory depression. The NAPRESSIM trial aims to answer this question.

**Methods/design:**

‘The use of low-dose, prophylactic naloxone infusion to prevent respiratory depression with intrathecally administered morphine’ trial is an investigator-led, single-centre, randomised, double-blind, placebo-controlled, double-arm comparator study. The trial will recruit 96 patients aged > 18 years, undergoing major open hepatopancreaticobiliary resections, who are receiving intrathecally administered morphine as part of a standard anaesthetic regimen. It aims to investigate whether the prophylactic administration of naloxone via intravenous infusion compared to placebo will reduce the proportion of episodes of respiratory depression in this cohort of patients.

Trial patients will receive an infusion of naloxone or placebo, commenced within 1 h of postoperative extubation continued until the first postoperative morning. The primary outcome is the rate of respiratory depression in the intervention group as compared to the placebo group. Secondary outcomes include pain scores, rates of nausea and vomiting, pruritus, sedation scores and adverse outcomes. We will also employ a novel, non-invasive, respiratory minute volume monitor (ExSpiron 1Xi, Respiratory Motion, Inc., [name]) to assess the monitor’s accuracy for detecting respiratory depression.

**Discussion:**

The trial aims to provide a clear management plan to prevent respiratory depression after the intrathecal administration of morphine, and thereby improve patient safety.

**Trial registration:**

ClinicalTrials.gov, ID: NCT02885948. Registered retrospectively on 4 July 2016.

Protocol Version 2.0, 3 April 2017.

Protocol identification (code or reference number): UCDCRC/15/006

EudraCT registration number: 2015-003504-22. Registered on 5 August 2015.

**Electronic supplementary material:**

The online version of this article (doi:10.1186/s13063-017-2370-0) contains supplementary material, which is available to authorized users.

## Background

Liver, pancreatic and biliary resections are common surgical procedures worldwide. However, the optimum modality of analgesia remains controversial [1–4]. Some centres utilise thoracic epidural analgesia (TEA) as part of their postoperative analgesic regimen [5–8] and the use of TEA has been advocated as improving outcomes, providing superior analgesia and increasing recurrence-free survival in patients undergoing resection of colorectal liver metastases [1, 7, 9–14]. However, others have raised concerns [15–17], namely: the theoretical risk of epidural haematoma in the setting of increased risk of coagulopathy, increased intravenously administered fluid volume associated with TEA, prolonged immobility, failure of analgesia [18] and increased length of stay [19] compared to available alternative methods of analgesia. Although the incidence of epidural haematoma is rare [20], mild-to-moderate coagulation abnormalities after major liver resection are not uncommon [21–23], and in this setting it is reasonable to assume an increased risk of haematoma. Coagulation abnormalities also affect timing of removal of the epidural catheter in patients post liver resection [17]. Some components of enhanced recovery programmes, such as early mobilisation and strict fluid balance, can be adversely affected by epidural analgesia [24, 25].

A number of studies have shown the benefit of intrathecally administered morphine (ITM) in this patient cohort [26–31]. The dose remains debatable, but the requirement for higher doses of ITM than in obstetric or pelvic procedures has been shown [32–34]. Unfortunately, at the doses required (up to 1 mg has been studied and shown to be effective), the risk of respiratory depression is well documented [35–37]. Rates of respiratory depression are variable in the academic literature (between 0.36% and 7.0%) [38–44], but there are methodological variances which may explain the difference in reported rates; also, there are few studies of homogenous patient groups. Even the definition of respiratory depression remains controversial [45, 46]. There is some consensus that patients receiving doses of ITM over 300 mcg should be monitored at a level above general ward level care, in order to monitor for, and treat, respiratory depression without any adverse outcome for the patient [47, 48]. The majority of hepatopancreaticobiliary anaesthetists in our centre routinely use a combination of ITM at a dose of 10 mcg/kg, administered prior to induction of anaesthesia, abdominal wall local anaesthetic blocks (transversus abdominus plane blocks and rectus sheath blocks) administered after induction under ultrasound guidance, and surgically positioned wound infiltration catheters placed at the end of surgery.

Apart from respiratory depression, the risk of nausea and vomiting, pruritus and urinary retention are significant following ITM [35, 49]. While not life-threatening, these complications are upsetting for patients and are considered to be significant events in the postoperative period [49, 50].

One suggested method of reducing respiratory depression and other side effects is the use of a prophylactic naloxone infusion. Naloxone has been reported in the academic literature as a reversal agent for morphine-induced respiratory depression since 1973 [51]. However, the bulk of publications refer to its use as a treatment rather than a prophylactic agent. Some publications address prophylaxis of respiratory depression, but available academic literature is mainly restricted to the obstetric setting [52, 53]. Two retrospective analyses in a urological surgery cohort (*N* = 35) and a gynaecological surgery cohort (*N* = 98) of patients have been published [54, 55] showing a good safety profile for the combination of higher doses of ITM with prophylactic naloxone infusion. These papers did not compare to a placebo group. No prospective data exist using this regimen in our study population.

Our study aims to investigate whether a similar prophylactic naloxone infusion in a cohort of patients undergoing major open hepatopancreaticobiliary resections with ITM will reduce the incidence of respiratory depression (primary) and other clinically significant side effects (secondary).

## Methods/design

### Trial design

This is an investigator-led, single-centre, randomised, double-blind, placebo-controlled, double-arm comparator study. It aims to investigate whether the prophylactic administration of naloxone via intravenous infusion compared to placebo will reduce the risk of respiratory depression to a clinically significant degree. The trial will recruit 96 patients aged 18 years or older, undergoing major open hepatopancreaticobiliary resections who will receive ITM 10 mcg/kg as part of a standard anaesthetic regimen, in St Vincent’s University Hospital, Dublin, Ireland.

### Participants

Participants will be those patients undergoing any major open hepatopancreaticobiliary resection in our university hospital hepatopancreaticobiliary surgery unit. Recruited patients will undergo surgery with standard anaesthetic management as shown in Fig. 1. They will also have an additional non-invasive monitor, the ExSpiron 1Xi (Respiratory Motion, Inc., [name]) applied. This will be used for data collection only, and no clinical decisions will be made based on its readings.

**Fig. 1 Fig1:**
[figure not shown]
Standard anaesthetic management. Schematic diagram showing standard anaesthetic management of open hepatobiliary surgical patients in our unit

### Inclusion and exclusion criteria

Patients who undergo major open hepatopancreaticobiliary resections and receive ITM 10 mcg/kg as part of their standard anaesthetic management. See Table 1.

**Table 1 Tab1:** Eligibility criteria for participants

Inclusion criteria	Exclusion criteria
> 18 years old at screening	Allergy/sensitivity to naloxone
Presenting for elective major open hepatopancreaticobiliary resection under general anaesthetic	Female subjects who are pregnant or breast feeding
Able/willing to give written informed consent and to comply with the requirements of the study	Received any other investigational medicine within the prior 2 months
	Receiving anticonvulsant medications
	Cardiac arrhythmia with uncontrolled rate
	History of chronic opioid use/chronic pain
	Contraindication to intrathecal injection
	Documented history of obstructive sleep apnoea
	Treating clinician does not have equipoise to randomise this patient into the study

### Setting

The trial will be carried out in the hepatopancreaticobiliary surgery unit of St Vincent’s University Hospital. Participants will be cared for in either the post-anaesthesia care unit (PACU) or the Bloomfield high-dependency unit (HDU) for the duration of the trial period. Nursing care will be at least a ratio of 1:2 for the duration of the trial. All data collected pertaining to the primary and secondary outcomes will be collected as part of the routine postoperative nursing care documentation.

### Outcome measures

The primary outcome of this trial is the rate of respiratory depression during the study period for patients receiving naloxone infusion compared to placebo. Respiratory depression will be diagnosed based mainly on criteria derived from the American Society of Anesthesiologist’s (ASA) ‘Practice Guidelines for the Prevention, Detection and Management of Respiratory Depression Associated with Neuraxial Opioid Administration’ [40] 2016 document. The criteria we will use are: respiratory rate < 10 and/or a decrease in SpO_2_ to < 92% and/or an increase in FiO_2_ required to maintain SpO_2_ > 92%. The primary outcome will be recorded as a dichotomous variable, recording any episode of respiratory depression during administration of the study infusion. Study infusion will be administered from within 60 min of extubation until 8:00 a.m. on the first postoperative morning.

### Secondary outcomes

Secondary outcomes will be recorded as the occurrence of the dichotomous variables presence or absence of pruritus and nausea/vomiting at any time over the monitoring period, and continuous outcomes will be assessed over the same time period.Incidence of pruritusPresence or absence of pruritus will be recorded on an hourly basis, along with the need for any rescue medication for treatment of pruritus
Incidence of nausea and vomitingPatients will be asked to report any incidence of nausea on an hourly basis and any episode of vomiting will be recorded. The use of any antiemetic agents, the frequency of administration and the total dose required will be recorded
Ramsey Sedation ScoreThe Ramsey Sedation Score will be recorded on an hourly basis. Any change in sedation score in the treatment arm will be assessed
Pain scoresWe use a numerical rating scale from 0 to 10 in assessing pain in our unit, and this will be recorded on an hourly basis
Requirement for supplemental fentanyl (rescue analgesia)Total dose of rescue intravenously administered fentanyl administered during the study period will be assessed
Patient overall satisfaction with analgesiaWe will utilise a simple Visual Analogue Scale, which will be scored at the end of the study period, by the investigator
Rate of respiratory depression associated with a Ramsey Sedation Score ≥ 3We will assess the respiratory depression parameters listed above, combined with Ramsey Sedation Scores
Rate of respiratory depression associated with a PaCO_2_ ≥ 50 mmHgWe will assess the respiratory depression parameters, combined with the 2-hourly PaCO_2_ results
Any differences in haemodynamic parameters between study groupsWe will compare heart rate (HR), systolic and diastolic blood pressures and need for any vasopressor support between the two groups
Major adverse events, adverse events and protocol deviations will be recorded and compared between the two groups

### Exploratory objective

To determine the accuracy of the Respiratory Motion ExSpiron 1Xi versus clinical observations in detecting respiratory depression in our patient population, we will collect the minute-volume data, and note all episodes of respiratory depression compared to the traditional diagnostic parameters listed above. We will also evaluate the relationship between minute volume and PaCO_2_ to determine if changes in minute volume are reflected by changes in PaCO_2_ levels. In view of the inaccuracy of clinical observations in diagnosing respiratory depression, this may add to the diagnostic armoury for improving diagnosis.Exploratory outcomes: minute volume○ Respiratory depression as diagnosed by ExSpiron manufacturer criteria – minute volume decreased to 40% predicted

### Interventions

Intervention in trial participants will include standard anaesthetic management as per Fig. 1, plus the addition of a study infusion postoperatively. The study infusion is an intravenous infusion of naloxone hydrochloride 20 mcg/mL, administered at a rate of 0.25 mL/kg/h (5 mcg/kg/h) or placebo (0.9% NaCl) at 0.25 mL/kg/h. Postoperative follow-up will be the same in both arms of the trial. Figure 2 shows the frequency and type of data collected. Patients will be monitored for 18 to 24 h post administration of ITM, exceeding the maximum risk period for respiratory depression. Study involvement ends at 8:00 a.m. the morning after surgery. All patients will have ITM administered prior to 2:00 pm on the day of surgery, meaning that the duration of monitoring in all patients is at least 18 h post administration of ITM, as is standard practice in our unit.

**Fig. 2 Fig2:**
[figure not shown]
Data collection. Schematic diagram demonstrating the data which will be collected, and the timing of that data collection. *All observations may be collected more frequently if clinically indicated

### Investigational product

Naloxone, the study medication, will be supplied to the St Vincent’s University Hospital pharmacy by Mercury Pharma Ltd. (Dublin, Ireland). Each 1-mL ampoule of solution contains 400 mcg (0.4 mg) naloxone hydrochloride present as naloxone hydrochloride dihydrate. This will be diluted to a concentration of 20 mcg/mL with 0.9% NaCl and presented as a clear, colourless, sterile solution for infusion. The study infusion is for clinical trial use only and can only be administered to the patient named on the drug label. The study infusion will be commenced within 1 h of extubating the patient and continued until 8:00 a.m. the morning after surgery. Unused study solution can be disposed of by nursing staff, in compliance with standard practice for disposing of unused medications/intravenously administered fluids. Placebo is 0.9% NaCl. Both the active infusion and placebo will be prepared according to the randomisation schedule in the hospital sterile isolator department.

### Screening and consent

Theatre lists will be reviewed in advance of the day of surgery to assess for patients having eligible surgical procedures. These patients will then be screened either on the ward or in the pre-operative assessment clinic in order to assess if the individual patient meets eligibility criteria. The patient will be provided with a patient information leaflet and allowed time to read through it. On the morning of surgery the patient will be given the opportunity to ask questions, prior to discussing and signing consent.

### Randomisation

Trial treatment will be allocated between study drug and placebo in a ratio of 1:1 according to variable block randomisation, with block sizes of 4 and 6. The randomisation schedule will be drawn up by a trial statistician using the statistical software R (R Core Team, 2016). The randomisation schedule will consist of a list of randomisation codes, each with a corresponding treatment assignment.

Randomisation will be implemented by the study pharmacist. All eligible consenting patients will be randomised on the morning of surgery. The treating clinician will assign each patient a randomisation code and will inform the study pharmacist of this code. The study pharmacist will use the pre-prepared randomisation schedule to determine treatment allocation of a patient (study drug or placebo) according to the patient’s randomisation code. They will not inform the treating physician, nursing staff or allocated patient.

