### Blinding

The study will be conducted as a blinded trial. Patients, treating physicians and nursing staff will be unaware of the treatment allocations. To maintain blinding of these trial team members, some of the trial staff will be unblinded; specifically, the study pharmacist and the trial statistician.

The study pharmacist will prepare either the study drug or the placebo solution, according to the randomisation schedule. The infusions will be prepared in the aseptic unit on the morning of surgery and will be dispatched to the PACU to be commenced within 1 h of extubation. Both study drug and placebo solutions will appear identical: clear in colour, packaged and labelled identically by the trial pharmacist.

Procedures will be put in place for emergency unblinding. The blinding can be broken in the event of a serious adverse event (SAE) or at request of the treating clinician to the study principal investigator (PI), due to clinical need. In the event of an allergic reaction where the allergen is unclear, even though the incidence of anaphylactic reaction to naloxone is rare, the study infusion should be stopped immediately and the treatment allocation of the patient will be unblinded.

For the purposes of emergency unblinding, a copy of the randomisation schedule will be stored in sequentially numbered opaque sealed envelopes (labelled with randomisation codes), in a cupboard in the administration office of the intensive care unit (ICU), in very close proximity to PACU. The PI and ICU nursing managers will be aware of the location of the randomisation schedule in the event of an emergency.

The study PI will know the location of the subject randomisation codes and will be contacted in any emergency situation to assist with unblinding the allocation. The contact details for the PI will be recorded in the clinical notes and on the anaesthetic sheet in the clinical notes. Nursing staff will be made aware of the location of these contact details during handover of the patient from the operating theatre.

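### The treating clinician assigns the code that fixes treatment, and a code-labelled copy of the whole schedule is kept near the PACU: an avoidable exposure of allocation concealment

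*Protocol article*

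**What the plan says.** All references are to the protocol article.

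- **Randomisation, the list.** The trial statistician prepares it in advance, 1:1, in blocks of 4 and 6. "The randomisation schedule will consist of a list of randomisation codes, each with a corresponding treatment assignment".
- **Randomisation, the roles.** The section opens its account of the procedure with "Randomisation will be implemented by the study pharmacist". It then says: "The treating clinician will assign each patient a randomisation code and will inform the study pharmacist of this code". The pharmacist looks the code up to find the treatment. On disclosure: "They will not inform the treating physician, nursing staff or allocated patient".
- **Inclusion and exclusion criteria, Table 1.** One exclusion reads: "Treating clinician does not have equipoise to randomise this patient into the study".
- **Blinding.** For emergencies, "a copy of the randomisation schedule will be stored in sequentially numbered opaque sealed envelopes (labelled with randomisation codes), in a cupboard" in the ICU administration office, close to the PACU. "The PI and ICU nursing managers will be aware of the location of the randomisation schedule in the event of an emergency". The only staff meant to be unblinded are the study pharmacist and the trial statistician.

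**The concern.** Concealment is strongest when the person who can decide whether a patient enters the trial has no hand in choosing the list entry and no route to upcoming entries. Here the matching of patient to code is given to the treating clinician, who also has a subjective veto on entry. The key to future codes is stored near the clinical area.

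If an upcoming allocation became known, the veto or the choice of code could be used, even unconsciously, to direct higher-risk patients to one arm. If a current patient's allocation became known, bedside recording would no longer be blind. The primary outcome includes a rise in the oxygen fraction needed to hold saturation, which involves some bedside judgement. Pruritus, nausea, sedation and pain are recorded hourly, and the Setting section says that the outcome data come from routine nursing documentation.

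**Working it through.** The point is procedural and the plan gives no figure for it, so the check sets the statements side by side.

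1. **What fixes treatment?** The schedule is a list of codes, each already paired with a treatment. Once a patient has a code, the treatment is determined, and the pharmacist's step is a look-up.
2. **Who matches patient to code?** The treating clinician, by direct statement. This sits awkwardly with the statement, in the same paragraph, that the pharmacist implements randomisation. The pharmacist implements the code-to-treatment step and the clinician the patient-to-code step.
3. **What say does that clinician have over entry?** The equipoise exclusion in Table 1. The Screening and consent section does not name who screens, so nothing wider can be attributed to the clinician.
4. **What does the emergency copy contain?** It is described as a copy of the schedule, and the schedule is the full list. Nothing limits the copy to patients already enrolled, so as described it includes codes not yet used.
5. **What stands between that copy and a reader?** An opaque seal on each envelope. The label shows the code and not the treatment. The treating clinician knows the patient's code, so anyone with that code and an opened envelope could link patient to treatment, before or after enrolment.
6. **Can allocations be guessed without opening an envelope?** Not with certainty. For a block of size 2m with all earlier allocations and the block size known, the mean number of fully determined assignments is 2m/(m+1):
   - Block of 4: 4/3 = 1.33, or 33% of the block.
   - Block of 6: 6/4 = 1.5, or 25% of the block.

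   Both conditions fail while block sizes vary and the blind holds. Guessing is therefore not the weak point.

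Steps 1 to 5 leave two features that the article states outright: the clinician's role in assigning codes, and a full copy of the list outside pharmacy. With both in place, the seals are the remaining barrier.

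**The case against.** The case for the plan is substantial. The envelopes are opaque, sealed and numbered in sequence, so a missing one could be noticed. A code tells its holder nothing. Only the pharmacist converts it, and does not disclose the result. Patients are randomised after eligibility and consent, and the two infusions look and are labelled alike. Knowledge of the storage place is attributed to the principal investigator and ICU nursing managers, not to treating clinicians in general. A clinician wishing to steer would have to find the envelopes, break a seal on an unused code and then act on it. All of this stands.

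It also rules out several stronger readings that a reader might infer:

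- *Concealment fails as soon as someone looks.* Looking shows only a code; a seal must be broken.
- *The clinician decides eligibility.* The article gives that role only the equipoise exclusion.
- *Codes are used out of order, or the cupboard is unlocked and unlogged.* The article is silent on order, lock and log. An article may leave such details to the full protocol, so that silence is not a finding.
- *A few steered patients would overturn the result.* One patient is 1/48 = 2.1 percentage points of an arm, but treating each steered patient as a certain event assumes what is not known. The article supports no estimate of how often steering would occur or how far risk would differ.

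What the objection does not remove is who assigns the code and what is stored outside pharmacy. Both are stated procedures, not omissions.

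**Conclusion.** The concern holds as one of avoidable exposure. The stated procedure gives the patient-to-code step to a clinician with some discretion over entry, and keeps a code-labelled copy of the schedule, with no stated restriction to enrolled patients, near the unit where the infusions are started. Concealment of future allocations and the blind for current patients then depend on the seals staying intact. Nothing in the article suggests that a seal was broken or an allocation steered, and the effect on the result cannot be quantified from it.

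The conclusion rests on two readings: that a copy of the schedule means the whole list, and that the clinician who assigns the code is the one named in the equipoise exclusion, since both places use the same title. If the full protocol already has the pharmacist issue codes in order and limits the ICU set to enrolled patients, only the article's wording needs correcting.

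**What to change.** **Randomisation section.** The clinician tells the pharmacist only that an eligible patient has consented. The pharmacist logs the enrolment irrevocably and then issues the next unused code in sequence. This also makes the section consistent with its statement that the pharmacist implements randomisation.

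**Blinding section.** Envelopes for unused codes stay in pharmacy. Once a patient is enrolled, only that patient's sealed envelope goes to the existing ICU office location, under lock. Any opening is logged, and the seal is checked when the envelope returns to pharmacy. The envelope should not travel to the bedside with the infusion, because that would put the key closer to the staff who record the outcomes.

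**Cost.** A pharmacy log and one envelope transfer per patient. The pharmacist already holds the schedule and prepares each infusion on the morning of surgery. Emergency unblinding access is unchanged. Recruitment was still under way when the article was written (Current status), so the change could apply to the patients still to be enrolled.
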